### Statistical analysis

Primary analysis will be performed on all patients included in the cohort. Only patients who withdrew consent will be excluded. Patients who decided to stop tracking or who were lost to follow-up will be included in the analysis. Any missing value will be replaced by the previous value (the last value carried forward method). Sensitivity analyses for missing values will be conducted, for example, using a multiple imputation (MICE, multiple imputation by chained equations [59]. All tests will be bilateral formulation, with a risk of type I error of 5 %.

Calculating the number of subjects required is based on the primary endpoint, i.e., the impact and the risk factors on one year all-cause mortality. The study of the literature and the completion of the preliminary inquiry (conducted in December 2009) in 14 centers that participated to the study conduct us to assume a 1-year mortality after ICU discharge of 18 %. To ensure detection with a power of 80 % of binary prognostic factors with a prevalence of 33 % and an expected OR of 1.5 and a probability of death of approximately 18 %, 1636 patients should be included in this study [60]. Assuming a rate of refusal and/or follow-up losses of 10 %, the number of patients to be included in the one-year follow-up amounts to 1800. The expected in-ICU mortality rate is 25 %. Thus, taking into account these results, the number of patients to be included is 2250.

The primary analysis will be based on the research of the determinants of 1-year mortality of patients included in the FROG-ICU (i.e., ICU patients who needed mechanical ventilation for more than 24 h and/or treatment with a positive inotropic agent over 24 and who were discharged alive from the ICU) among clinical and biological variables and biomarkers of common interest (i.e., troponins, natriuretic peptides). The regression model used will be the logistic model. The log-linearity of the quantitative variables will be systematically evaluated, and, if appropriate, variable transformations will be performed. A selection model process will be performed using stepwise selection method. The selection process model will be further validated by bootstrap [61]. The existence of any collinearities will be observed, and a test of goodness of fit will be performed using the test and the van Cessie Houwelingen method [62]. Finally a cross-validation procedure will be performed. The measures of association will be provided, with odds ratios and confidence intervals at 95 %. An estimate of related risks will also be conducted. Finally, the overall incidence of 1-year mortality will be estimated at a confidence interval of 95 %.

As it is now recognized that highlighting the statistically significant association between new biomarkers and patient outcomes is not sufficient to demonstrate the interest of these biomarkers in terms of risk prediction [63–65]. We will use the proposed methodology of Pencina et al., which has been used in multiple articles of application. For each biomarker of interest, the net reclassification improvement (NRI) and integrated discrimination improvement (IDI) will be calculated, and comparisons between different biomarkers will be performed [64].

Regarding quality of life, a strategy similar to that outlined for the 1-year mortality analysis will be used to assess its impact and to highlight the predictors of impaired QoL at 6 months or 1 year. QoL will be estimated using the SF-36 score (ranging from 0 to 100) [66]. Altered QoL is considered when SF-36 is lower than 50. In addition, the value of the SF-36 measured in the FROG ICU study will be compared with the values that are typically found in healthy populations of the same age and sex. Interaction between quality of life and social life will be assessed by using information from the social questionnaire.

Last, regarding stress and anxiety, as previously described, IES-R higher than 30 will define post-traumatic stress disorder [58] and HADS higher than 8 will defined anxiety [55]. Similarly, analyses will consist in seeking to identify risk factors of stress and anxiety after ICU discharge.

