## Methods and Design

### Study design

The French and European Outcome Registry in Intensive Care Units (FROG ICU) study is a prospective, observational, multicenter cohort study, designed to assess the incidence and to identify the risk factors of mortality during the year following discharge from the ICU. The study will be conducted in France and in Belgium in accordance with Good Clinical Practice, Declaration of Helsinki 2002, validated by the ethical committee (Comité de Protection des Personnes - Ile de France IV, IRB n°00003835. Comission d’éthique biomédicale hospitalo-facultaire de l’hôpital de Louvain, IRB n°B403201213352) and was registed on ClinicalTrials.gov (NCT01367093). The study consists of two phases (Fig. 1): initially, all patients admitted to any of the participating centers during the recruitment period will be screened for the eligibility criteria listed below; subsequently, all patients included in the study who survive to ICU discharge will be followed up for one year through a telephone call and postal questionnaires at 3, 6 and 12 months.

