### Participants

The study will involve 28 medical, surgical or mixed ICUs in 19 hospitals. The study cohort will include all consecutive patients who are admitted in ICU to any of the participating centers during the recruitment period when the following inclusion criteria are met: invasive mechanical ventilation support for at least 24 h and/or treatment with a positive inotropic agent (except dopamine) for more than 24 h. Because the ethical committee waived the need for written consent, all patients and/or next of kin will be informed and will orally consent to participate; consent was documented in the medical record by the investigator. Exclusion criteria are the following: less than 18 years old; severe head injury (initial Glasgow Coma Scale < 8) or brain death or a persistent vegetative state; pregnancy or breastfeeding; transplantation in the past 12 months; not expected to survive or to leave the hospital; and/or no social security coverage.

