### Study objectives

#### Primary objective

The primary purpose of this study is to assess the incidence of all-cause mortality in the year following an ICU stay and to identify the factors associated with mortality; those factors include both the clinical-biological factors and the ICU risk scores.

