All patients included in the study population who survive to ICU discharge will be followed up for one additional year or until death, except for severely disabled subjects (Glasgow Outcome Scale < 4 at discharge). One-year outcome will be evaluated through data collection at 3, 6 and 12 months after ICU discharge. At those time points, patients will be contacted by telephone, and information about vital status (patient dead or alive), re-hospitalization, and cardiovascular morbidity will be recorded. For patients lost of follow-up, the vital status will eventually be checked through the national health services records when available. In addition, 4 follow-up questionnaires will be submitted to the study population: the Hospitalization Anxiety and Depression Scale (HADS) [55] and the Short Form-36 (SF-36) [56, 57] at discharge and at 3, 6, and 12 months after and the Impact of Event Scale-Revised (IES-R) [58] at 3, 6 and 12 months; a social questionnaire for assessing patients’ social environments (actual occupation, resumption of activity, level of income, marital status,…) will be submitted at 3 months after discharge.

A biological collection will be created with blood (3x10 ml in EDTA and aprotinin) and urine (10 ml) samples collected at two different time points: admission and discharge. The biological collection will allow for the measurement of novel biomarkers in a central laboratory. Table 3 lists the biomarkers with potential interest for the risk stratification of patient who survive an ICU stay.

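### The opening sentence of Statistical analysis sets the primary analysis on all included patients, ICU deaths among them, although the rest of the protocol intends ICU survivors, and survivors left out of follow-up stay in the analysis with no outcome collected

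*Protocol article*

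**What the plan says.** All references are to the protocol article.

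- **Participants** defines the cohort at the ICU stay: "The study cohort will include all consecutive patients who are admitted in ICU to any of the participating centers during the recruitment period", subject to the ventilation or inotrope criterion.
- **Statistical analysis, first paragraph**, sets the population: "Primary analysis will be performed on all patients included in the cohort". It adds "Only patients who withdrew consent will be excluded". Patients who stop follow-up or are lost stay in, and a missing value takes the previous value. Multiple imputation is offered as a sensitivity analysis.
- **Statistical analysis, second paragraph**, assumes 18% mortality in the year after discharge and 25% mortality in the ICU, with 1636 patients needed, 1800 entering follow-up and 2250 included.
- **Statistical analysis, third paragraph**, describes the primary analysis again and explains the included patients as those who met the entry criterion "and who were discharged alive from the ICU". It closes by promising the *overall* incidence of one-year mortality, without a denominator.
- **Primary objective**: "to assess the incidence of all-cause mortality in the year following an ICU stay". **Study design**: "all patients included in the study who survive to ICU discharge will be followed up for one year".
- **Data collection and biological samples**: "All patients included in the study population who survive to ICU discharge will be followed up for one additional year or until death", with an exception for patients whose Glasgow Outcome Scale at discharge is below 4.

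**The concern.** The one sentence that expressly fixes the primary population and its only exclusion names a set that does not match the objective. An analyst who followed it literally would put patients with no post-discharge period into a model of post-discharge death. Discharge examinations and samples cannot exist for them, and the previous-value rule would fill those fields with earlier ICU measurements.

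The word *overall* adds to the risk. The Background uses overall mortality for ICU plus post-ICU deaths (pooled 33.4%) and reports it beside post-ICU mortality (pooled 18.8%). The incidence estimate thus borrows the term for the quantity that the study is not about.

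The second problem concerns the survivors. Those with a Glasgow Outcome Scale below 4 have no planned outcome collection, yet the only permitted exclusion is withdrawn consent. They stay in the denominator without a way for their deaths to reach the numerator. They are severely disabled, so their mortality is unlikely to be lower than that of the other survivors.

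**Working it through.** **1. Does the included count contain ICU deaths?** The protocol's steps reproduce as multiplications:

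- 1636 × 1.10 = 1799.6, stated as 1800 entering follow-up.
- 1800 × 1.25 = 2250, stated as the number to be included.

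The difference, 2250 − 1800 = 450, is the allowance for ICU deaths. In this protocol, then, being included means entered during the ICU stay, and the set named in the opening sentence contains ICU deaths.

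**2. Which ICU mortality applies?** The text states 25%. The step from 1800 to 2250 implies 450 / 2250 = 20%. Both are carried below.

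**3. One-year mortality under each denominator.** With p_ICU the ICU mortality and p_post = 0.18 the mortality in the year after discharge:

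mortality among all included = p_ICU + (1 − p_ICU) × p_post

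| Denominator | ICU mortality | Calculation | Result |
|---|---|---|---|
| Discharged alive | not applicable | 0.18 | 18% |
| All included | 20% (implied) | 0.20 + 0.80 × 0.18 | 34.4% |
| All included | 25% (stated) | 0.25 + 0.75 × 0.18 | 38.5% |

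At 25%, ICU deaths number 2250 × 0.25 = 562.5 and later deaths 1687.5 × 0.18 = 303.75. ICU deaths would be 0.25 / 0.385 = 65% of events. At 20% they would be 0.20 / 0.344 = 58%. Under either figure most events would be ICU deaths, if those were counted.

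Sampling error does not blur the difference. The 95% interval is about 16.2% to 19.8% for 18% of 1800, and about 36.5% to 40.5% for 38.5% of 2250.

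**4. Survivors with a Glasgow Outcome Scale below 4.** Let g be their share of survivors and m their one-year mortality. If all are carried forward as alive, mortality among survivors is understated by g × m. The protocol gives neither quantity. If m were only the 18% assumed for survivors in general, each 1% of survivors in this group would cost 0.01 × 0.18 = 0.18 percentage points. A higher m costs proportionately more. The direction is certain as long as any of them die within the year.

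**5. The statements side by side.**

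| Place | Population |
|---|---|
| Statistical analysis, first paragraph | All included, less withdrawn consent |
| Statistical analysis, third paragraph | Included and discharged alive |
| Sample size | 18% after discharge; 1800 survivors followed |
| Study design | Survivors followed for one year |
| Data collection | Survivors followed, except Glasgow Outcome Scale below 4 |

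The first row stands alone in taking in ICU deaths. The last row is narrower than any stated analysis set.

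**The case against.** A fair defence is that the third paragraph resolves the matter. It is the more specific statement, it sits in the same section, and it says outright that the patients meant are those discharged alive. The opening lines deal with withdrawal, loss to follow-up and missing values, so their purpose may be only to say that nobody is dropped for incomplete follow-up. This stands as evidence of intent. It does not make the opening sentence correct, because Participants and the count of 2250 give being included another meaning.

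A reader might go further and infer that the headline result could well be reported as 38.5%. The documents do not support that. A patient who dies in the ICU has no year after discharge, so reaching 38.5% requires counting ICU deaths as events as well as adopting the wider set. The objective, the follow-up scheme, the 18% input and the third paragraph all point the other way. The 38.5% is also only one of two figures, since the protocol's own step from 1800 to 2250 gives 34.4%.

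A reader might also infer three rival analysis populations. That too is more than the text says: the Glasgow Outcome Scale exception is a follow-up rule, and the plan does keep patients with incomplete follow-up in the analysis. What remains is that these patients are analysed with no outcome sought. The records check in Data collection is planned for patients lost to follow-up, where records are available, and is not stated to cover this group. The multiple-imputation sensitivity analysis leaves the primary handling unchanged.

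**Conclusion.** The contradiction is real and should be corrected. The opening sentence of Statistical analysis is wrong as written, because the rest of the protocol shows that the primary analysis concerns patients discharged alive. The incidence estimate needs its denominator named. Counting ICU deaths would move it from 18% to between 34.4% and 38.5%, given the protocol's planning values and ICU mortality of 20% (implied) or 25% (stated). That range measures what the ambiguity could do; it is not a forecast of what will be reported.

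The gap for survivors with a Glasgow Outcome Scale below 4 would bias one-year mortality downward if the previous-value rule is applied to vital status as literally stated. Its size is unknown, because the protocol gives neither the share of survivors in this group nor their mortality.

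**What to change.** 1. In the first paragraph of Statistical analysis, state that the primary analysis set is all included patients discharged alive from the ICU, with time zero at ICU discharge and withdrawn consent as the only exclusion.
2. In the third paragraph, give the incidence estimate that same denominator and drop the word *overall*. Report ICU mortality and overall mortality among all included patients separately, as descriptive figures.
3. Reconcile Data collection with Statistical analysis. Preferably extend the vital-status check, by call or by national records where available, to survivors with a Glasgow Outcome Scale below 4. If that is not possible, exclude them explicitly, report their number, and limit the conclusion to the remaining survivors.

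Items 1 and 2 cost wording only. Item 3 goes beyond wording: it adds a small vital-status check for a group that the protocol does not now follow, or, in the fallback, narrows the population to which the result applies.

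### Excluding patients who withdraw consent, while keeping those who stop tracking, can bias one-year mortality, in a direction that depends on the leavers' remaining risk

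*Protocol article*

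**What the plan says.** The Statistical analysis section sets the rule for the primary analysis: "Only patients who withdrew consent will be excluded. Patients who decided to stop tracking or who were lost to follow-up will be included". It then replaces any missing value by the last value carried forward. Sensitivity analyses are planned: "Sensitivity analyses for missing values will be conducted, for example, using a multiple imputation".

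Three other places bear on this:

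- **Participants**, on consent: "all patients and/or next of kin will be informed and will orally consent to participate".
- **Data collection and biological samples**, which plans telephone contacts at 3, 6 and 12 months and adds: "For patients lost of follow-up, the vital status will eventually be checked through the national health services records when available". This sentence names patients lost to follow-up. The Statistical analysis section lists patients who stop tracking as a separate group, and the article does not say whether the records check covers them.
- **Primary objective and Statistical analysis**, which make the incidence of one-year mortality, with a 95% confidence interval, a main output. The determinants analysis is in patients discharged alive from the ICU.

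**The concern.** The rule removes the patient, not merely the follow-up after withdrawal. Someone who withdraws at a follow-up call has survived to that call. Dropping that person discards observed survival time and selects on an event that occurs after enrolment and requires having lived long enough. If leavers then die at a lower rate over the remaining months than the cohort does over the whole year, the mortality estimate rises.

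A similar request, to stop being tracked, gets the opposite treatment: the patient stays in the denominator. Read literally, the carry-forward rule covers any missing value, so an untraced patient's last status, alive, would stand at one year. That pulls the estimate down. The same behaviour can therefore move a primary estimate either way, according to the category in which it is recorded.

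**Working it through.** **Inputs from the article.** 2250 patients to include; in-ICU mortality 25%; one-year mortality after discharge 18%; refusal and/or follow-up losses 10% combined.

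**Assumptions, not in the article.** The withdrawal rate (2%, 5% or 10% of ICU survivors, where 10% uses the whole stated allowance); leaving at the 3-month call; half of the year's deaths occurring by then; leavers at average remaining risk.

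**Base.** ICU survivors N = 2250 × 0.75 = 1687.5, about 1688. The article plans for 1800 in follow-up; the percentages below depend on the share leaving, so the choice hardly matters. Deaths D = 0.18 × 1688 = 303.84. The interval half-width is 1.96 × √(0.18 × 0.82 / 1688) = 1.8 points, and also 1.8 at N = 1800.

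**Remaining risk after month 3.** r = 0.09 / 0.91 = 9.9%.

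**Formulas**, with W leavers:

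- excluded: (D − W·r) / (N − W)
- kept and carried forward as alive: (D − W·r) / N
- kept and traced: D / N = 18.0%

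| Share leaving | W | Later deaths W·r | Excluded | Carried forward as alive | Traced |
|---|---|---|---|---|---|
| 2% | 34 | 3.36 | 300.48/1654 = 18.2% | 300.48/1688 = 17.8% | 18.0% |
| 5% | 84 | 8.31 | 295.53/1604 = 18.4% | 295.53/1688 = 17.5% | 18.0% |
| 10% | 169 | 16.71 | 287.13/1519 = 18.9% | 287.13/1688 = 17.0% | 18.0% |

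**Separating the two effects.** At 10% leaving, the gap between the labels is 1.9 points. Exclusion accounts for +0.9 and carrying alive forward for −1.0. At 5%, the parts are +0.4 and −0.5.

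**Direction of the exclusion bias.** Excluded minus true = W × (0.18 − r) / (N − W). The sign is that of 0.18 − r:

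| Leavers' remaining one-year risk | 1% leave | 5% leave | 10% leave |
|---|---|---|---|
| None die (upper bound) | 18.2% | 18.9% | 20.0% |
| 9.4% (leaving at 6 months, constant hazard) | 18.1% | 18.5% | 19.0% |
| 13.8% (leaving at 3 months, constant hazard) | 18.0% | 18.2% | 18.5% |
| 18% (leaving at discharge, average risk) | 18.0% | 18.0% | 18.0% |
| 30% (sicker leavers) | 17.9% | 17.4% | 16.7% |

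To reverse the sign, month-3 leavers need more than 0.18 / 0.099 = 1.8 times the average remaining risk if half the deaths fall early, or 0.18 / 0.138 = 1.3 times under a constant hazard.

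**Does censoring repair it?** Under the base assumptions, Kaplan-Meier gives 1 − 0.91 × (1 − 0.0989) = 18.0%, whatever share leaves at month 3.

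**The case against.** The strongest reply is that excluding patients who withdraw consent may be an ethical or legal requirement, and that the article, as a condensed document, may leave the definitions of the two requests to the full protocol. Both points are fair. The absence of definitions is not counted here as a fault, and any remedy must still remove patients whose data have to be deleted. The article nevertheless states the exclusion and retention rules outright, and definitions elsewhere would not undo the selection they create.

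Several stronger readings are tempting and are not supported:

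- *The rule inflates mortality.* Direction is not established. The bias is nil for average-risk withdrawal at discharge and reverses for sicker leavers. Surviving the ICU is common to everyone in the post-discharge denominator, so it cannot itself produce the bias; only withdrawal later in the year does so at average risk.
- *Only living patients can leave.* Next of kin may consent, and nothing says that they cannot withdraw.
- *The exclusion shifts the estimate by as much as the interval half-width.* The 1.9-point gap at 10% leaving includes the carry-forward effect. Exclusion alone is about half of it.
- *Risk-factor odds ratios are biased.* Exclusion that depends on outcome alone, or on modelled covariates alone, does not bias logistic odds ratios. Withdrawal would have to depend jointly on the factor and on survival, which is possible but not shown.
- *Sites will code the same request differently.* The article uses two categories; inconsistent coding is a possibility, not a documented fact.

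The records check and the planned multiple imputation also soften the problem for retained patients. They do nothing for patients who have been excluded.

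**Conclusion.** The point stands in a limited form. Complete removal of patients who withdraw during follow-up can bias one-year mortality, and the opposite handling of those who stop tracking makes the estimate sensitive to the label. With 9.9% remaining risk at month 3, exclusion alone adds about 0.4 points if 5% leave and 0.9 if 10% leave, at most half of the 1.8-point interval half-width. If nobody who left died, the ceiling at 10% would be 2.0 points. At 1 to 2% leaving the effect is small.

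These sizes rest on assumed rates, timing and risk; the article supplies none of them. The concern is with the incidence estimate, and no effect on the risk-factor model has been demonstrated. The change is still worth making, because it is cheap and the affected quantity is a primary output.

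**What to change.** Apply one rule to both requests:

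1. Keep data up to the date of withdrawal or of stopping follow-up wherever consent and the ethics approval permit. Remove only patients who require deletion of their data.
2. Extend the national-records check explicitly to patients who stop tracking and to those who withdraw, unless they object to it.
3. Estimate one-year mortality by Kaplan-Meier, censoring at last known vital status, instead of carrying alive forward. This assumes that leavers have average remaining risk, so tracing should come first.
4. Report the number and timing of withdrawals, and bound the incidence with removed patients counted all alive and then all dead. If the 84 patients in the 5% scenario had to be removed, the bounds would be 295.53/1688 = 17.5% and (295.53 + 84)/1688 = 22.5%. They are wide, which is a reason to keep removals few.

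The cost is a change of wording, one electronic case report form field to separate no further contact, no records check and deletion of data, and patient information stating that data already collected are kept unless the patient objects.

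### The primary last-value-carried-forward rule counts patients with unresolved vital status as one-year survivors and fills missing discharge biobank markers with admission values

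*Protocol article*

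**What the plan says.** All of this is in the protocol article.

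- **Missing data (Statistical analysis).** "Any missing value will be replaced by the previous value (the last value carried forward method". The rule is general and belongs to the primary analysis.
- **Analysis set (same section).** "Patients who decided to stop tracking or who were lost to follow-up will be included in the analysis". Only withdrawal of consent removes a patient.
- **Model and estimate (same section).** "The regression model used will be the logistic model", and "the overall incidence of 1-year mortality will be estimated at a confidence interval of 95" per cent.
- **Sensitivity (same section).** "Sensitivity analyses for missing values will be conducted, for example, using a multiple imputation".
- **Outcome ascertainment (Data collection and biological samples).** "One-year outcome will be evaluated through data collection at 3, 6 and 12 months after ICU discharge". For patients lost to follow-up, "the vital status will eventually be checked through the national health services records when available".
- **Biobank (same section).** Blood and urine are "samples collected at two different time points: admission and discharge".

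**The concern.** The primary outcome is death within one year, analysed as yes or no in a model without censoring. Follow-up starts when the patient leaves the ICU alive, so the last known vital status of anyone later lost is necessarily alive. Carrying it forward turns unknown into survived. The error in the incidence has one direction and does not shrink with sample size, and incidence is half of the primary objective. The other half, the risk factors, is affected if loss is related to the factor under study.

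For predictors, the biobank has only two sampling times, so the only earlier value for a missing discharge sample is the admission one. The Background section motivates the study by measuring biomarkers at ICU discharge. Filling gaps with acute-phase values mixes two clinical states in one variable.

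**Working it through.** **Inputs from the article (Statistical analysis):** one-year mortality 18%; refusal and/or follow-up loss 10%; 1800 patients in follow-up (1636 × 1.10 = 1799.6); factor prevalence 33%; odds ratio 1.5. The article gives no figure for the effect of the missing-data rule, so there is none to reproduce.

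**Assumptions (not in the article):** the unresolved share d, the mortality m of unresolved patients, the split of loss by factor, and the share and accuracy of filled biomarker values. Loss is taken to occur soon after discharge. Later loss misses only deaths after the last contact, so the effect is smaller.

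**1. Incidence.** With 18% mortality among patients whose status is known:

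- true risk = (1 − d) × 18% + d × m
- reported risk = (1 − d) × 18%
- shortfall = d × m

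| d unresolved | Reported | Shortfall, m = 18% | m = 27% | m = 36% |
|---|---|---|---|---|
| 10% | 16.2% | 1.8 points | 2.7 | 3.6 |
| 5% | 17.1% | 0.9 | 1.35 | 1.8 |
| 2% | 17.6% | 0.36 | 0.54 | 0.72 |

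For comparison, the 95% half-width at N = 1800 is 1.96 × √(0.162 × 0.838 / 1800) = 1.70 points.

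**2. Odds ratio.** Take 18% as the overall risk. The group risks p0 (without the factor) and p1 (with it) must satisfy 0.67 × p0 + 0.33 × p1 = 0.18 with an odds ratio of 1.5, which gives p0 = 0.1595 and p1 = 0.2216. If the lost die at their own group's rate, the apparent risks are p0(1 − d0) and p1(1 − d1).

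- Loss 7.5% without the factor, 15% with it: 0.1475 and 0.1884; odds 0.1731 and 0.2321; odds ratio **1.34**.
- Split reversed (15% and 7.5%): 0.1356 and 0.2050; odds 0.1568 and 0.2578; odds ratio **1.64**.
- Equal loss (10% and 10%): 0.1436 and 0.1994; odds 0.1676 and 0.2491; odds ratio **1.49**.

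The planned 1636 is matched more closely if 18% is read as the risk in patients with the factor (12.8% without it; formula result 1653). On that reading the three odds ratios are 1.35, 1.64 and 1.49, so the conclusion does not depend on it.

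**3. Discharge biobank marker.** Suppose a fraction f of discharge values is replaced by admission status, with sensitivity se and specificity sp for the true discharge status and no further relation to death. The effective sensitivity is 1 − f + f × se, and likewise for specificity. For a true odds ratio of 1.5, and se/sp of 0.8/0.6 or 0.7/0.7:

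- f = 10%: 1.45 to 1.46
- f = 20%: 1.41 to 1.42
- f = 30%: 1.37 to 1.38

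**The case against.** Five points can be made for the plan.

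- **Records check.** Only patients whose status stays unknown after the national records check are miscounted, and 10% combines refusal with loss. This stands: 10% is an upper value, and at 2% the incidence error is small. But the check is conditional on availability, and no text exempts what remains from the rule.
- **Multiple imputation is planned.** It is, as one example of a sensitivity analysis. It would show the problem without changing the primary estimate.
- **The rule may be meant for repeated clinical measurements only.** That is possible, but the text says any missing value and in the same place keeps lost patients in the analysis.
- **Routine markers and SOFA** are also recorded during the stay, so a later in-stay value may be carried forward. This stands: the admission fill is certain only for biobank samples, and novel biomarkers are a secondary objective.
- **Kaplan-Meier assumes uninformative censoring.** If 10% are lost early and die at 30%, the truth is 0.9 × 18 + 0.1 × 30 = 19.2%, while censoring gives about 18%. This also stands. It is still closer than 16.2%, and it is why a sensitivity analysis for higher mortality in the lost is needed.

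Three stronger readings are tempting but unsupported. A reader might infer that odds ratios are always attenuated and power lost. The article does not say which patients are lost more often, and power follows the odds ratio: at N = 1800 it is 85% with equal 10% loss, 66% with 8% without and 14% with the factor, and 96% with 12.5% and 5%. A reader might infer that a patient with a missing admission value drops out of the model. The rule cannot fill that value, but the article does not say what happens next, and such detail commonly sits in the full plan. A reader might also infer that the logistic model must be abandoned; it can be kept.

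**Conclusion.** The rule is wrong as written for vital status. Every unresolved patient becomes a one-year survivor, and the reported incidence is too low by d × m: 1.8, 0.9 or about 0.4 points at 10%, 5% or 2% unresolved with equal mortality, and more if the lost die more often. At the upper value the error is as large as the sampling half-width. The direction is certain; the size depends on how many patients the records leave unresolved, which the article does not give.

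For odds ratios, no direction can be claimed. The bias is negligible if unresolved loss is unrelated to the factor and material if it differs about twofold, as in the examples. For discharge biobank markers, mixing in admission values is certain wherever a discharge sample is missing and an admission sample exists. The illustrated dilution rests entirely on assumed inputs.

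**What to change.** Remove the last-value rule from the primary analysis and replace it as follows.

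- **Vital status.** Do not carry it forward. After the planned records check, handle unresolved patients in the planned logistic model by multiple imputation of one-year status or by inverse-probability-of-censoring weights.
- **Incidence.** Estimate it in a way that respects censoring, for example Kaplan-Meier at 12 months with a 95% confidence interval. Report the number unresolved.
- **Sensitivity.** Add an analysis in which unresolved patients have higher mortality than those followed.
- **Predictors.** Make the chained-equations imputation already named the primary method, with the outcome in the imputation model. Do not substitute admission values for discharge values.

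The cost is revised wording, modest extra programming and slightly wider intervals. No new data collection is needed: neither a switch to Cox regression nor a records query for every patient is required.
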